## Abstract

**Background:**

Most international guidelines recommend triple-therapy regimens consisting of a proton pump inhibitor, clarithromycin, and amoxicillin/metronidazole for at least 7 days for the eradication of *Helicobacter pylori*. However, the efficacy of 7-day clarithromycin-based standard triple therapy for *H. pylori* infection is currently unacceptable in Korea. In this study, we will compare the efficacy and safety of 7-day standard triple therapy, 10-day sequential therapy, and 10-day concomitant therapy for the first-line treatment of *H. pylori* infection in Korea.

**Methods/design:**

In this multicenter, investigator-blinded, randomized trial we are recruiting adult patients with *H. pylori* infection from 15 hospitals in Korea to determine whether sequential or concomitant treatment is superior to standard triple therapy. Patients are randomly assigned to receive either standard triple therapy (lansoprazole, amoxicillin, and clarithromycin) for 7 days, or sequential treatment (lansoprazole and amoxicillin for the first 5 days, followed by lansoprazole, clarithromycin, and metronidazole for another 5 days) for 10 days, or concomitant therapy (lansoprazole, amoxicillin, clarithromycin, and metronidazole) for 10 days. The primary outcome is the rate of *H. pylori* eradication in the intention-to-treat population.

**Discussion:**

The results of this study will be crucial for determining the optimal regimen for the primary treatment of *H. pylori* infection in Korea. This study will produce vital evidence that will lead to revisions to guidelines concerning first-line treatment regimens for *H. pylori* infection.

**Trial registration:**

Clinical Research Information Service (CRIS), Republic of Korea, KCT0001980. Registered on 25 July 2016.

**Electronic supplementary material:**

The online version of this article (doi:10.1186/s13063-017-2281-0) contains supplementary material, which is available to authorized users.

## Background

*Helicobacter pylori* infection causes peptic ulcers, gastric mucosa-associated lymphoid tissue lymphoma, and gastric cancer [1]. Most international guidelines recommended triple-therapy regimens consisting of a proton pump inhibitor (PPI), clarithromycin, and amoxicillin/metronidazole for at least 7 days for the eradication of *H. pylori* [2–4]. However, the eradication frequency of standard triple therapy has fallen to less than 80% in many countries because of the rising prevalence of clarithromycin resistance [5–7]. The rate of clarithromycin resistance is reported to be as high as 37.3% in Korea. Consequently, the first-line eradication rate of triple therapy has been shown to be 74% according to a national database [8, 9]. Despite this issue, the standard triple-therapy regimen is still recommended for first-line therapy in Korea according to the revised guidelines, and it is the only regimen reimbursed by the Korean National Health Insurance Service [10].

Several strategies, including bismuth-containing quadruple therapy and non-bismuth-containing quadruple therapy (either sequential or concomitant), have been proposed to increase the eradication rate in Korea [11–14]. Because the efficacy of sequential treatment, which consists of a PPI and amoxicillin for the first 5 days, followed by a PPI plus clarithromycin and metronidazole for another 5 days, appears to be less susceptible to clarithromycin resistance than triple therapy, it was expected to become the standard first-line treatment for *H. pylori* infection. A meta-analysis indicated that sequential therapy was more effective than 7-day triple therapy, but there are regional differences in the efficacy of this approach, owing to geographical variations in antibiotic resistance [15, 16]. Furthermore, the pooled eradication rates of sequential therapy as a first-line treatment are reported to be suboptimal in Korea [17]. Nonbismuth quadruple therapy is another alternative to concomitant therapy, and it is proven to work even when clarithromycin resistance is present [18]. Several randomized trials comparing sequential with concomitant treatment have indicated no significant differences, whereas sequential therapy was found to be slightly more effective in Central and South America [19, 20]. In a small number of randomized controlled studies in Korea, 10-day or 5-day concomitant therapy was shown to be more effective than standard triple therapy [21, 22]. Some retrospective studies have demonstrated that concomitant therapy is superior to standard triple therapy [23]. Concomitant and sequential therapies were demonstrated to be similarly effective in a few head-to-head comparison studies in Korea [13]. Despite these previous results, evidence supporting these conclusions is insufficient because no studies with an adequately rigorous design have been performed. With these considerations in mind, we designed the present nationwide, population-based, randomized controlled trial to compare the efficacy of 10-day concomitant therapy, 10-day sequential therapy, and 7-day triple therapy as first-line therapy for *H. pylori* infection in a Korean population.

## Methods/design

### Trial design and study setting

This study is designed as a multicenter, randomized, three-arm, superiority, parallel-group trial. Participants will be randomly allocated to the following three arms in a 1:1:1 ratio:
*Arm 1 (control arm):* The standard triple-therapy group will receive lansoprazole 30 mg, amoxicillin 1 g, and clarithromycin 500 mg twice daily for 7 days.
*Arm 2 (experimental arm 1):* The sequential therapy group will receive lansoprazole 30 mg and amoxicillin 1 g twice daily for the first 5 days, followed by lansoprazole 30 mg, clarithromycin 500 mg, and metronidazole 500 mg twice daily for the remaining 5 days.
*Arm 3 (experimental arm 2):* The concomitant therapy group will receive lansoprazole 30 mg, amoxicillin 1 g, clarithromycin 500 mg, and metronidazole 500 mg twice daily for 10 days.

Participants will be recruited from 15 hospitals in Korea (Samsung Medical Center, Chung-ang University Hospital, Yonsei University Severance Hospital, National Cancer Center, Bundang Seoul National University Hospital, Chungbuk National University Hospital, Chungnam National University Hospital, Chonnam National University Hospital, Chonbuk National University Hospital, Chilgok Kyungpook National University Hospital, Keimyung University Dongsan Hospital, Pusan National University Hospital, Kosin University Gospel Hospital, Jeju National University Hospital, and Hallym University Chuncheon Sacred Heart Hospital) (Fig. 1). The recruitment period began in November 2016 and will end in October 2018. We received approval to conduct this study from the institutional review boards of 15 nationwide hospitals. This investigator-initiated trial was approved by the Korean Food and Drug Administration and is registered at https://cris.nih.go.kr/cris (KCT0001980). A flow diagram of the trial is shown in Fig. 2.

**Fig. 1 Fig1:**
[figure not shown]
Map showing the geographic locations of the 15 participating study centers in Korea

**Fig. 2 Fig2:**
[figure not shown]
Study design

### Study subjects

Consecutive outpatients with *H. pylori* infection aged ≥ 19 years who have undergone endoscopic examination within the prior 3 months, agree to trial participation, and provide written informed consent fulfill the eligibility criteria and are invited to participate in the study. Exclusion criteria include a history of *H. pylori* eradication therapy; gastric surgery; abnormal liver function test or renal function test results on screening laboratory studies; antibiotic use within the prior 4 weeks; PPI use within the prior 2 weeks; histamine-2 receptor antagonist, aspirin, nonsteroidal anti-inflammatory drug, steroid, anticholinergic, prostaglandin analog, promotility drug, or sucralfate use within the prior week; use of drugs such as lovastatin, simvastatin, atorvastatin, indinavir, ritonavir, cyclosporin, terfenadine, cisapride, pimozide, astemizole, HIV protease inhibitors, and ergot alkaloids; allergic reactions to the study medications; and serious concomitant illnesses. In addition, we will exclude pregnant participants or participants who plan to become pregnant as well as patients participating in other clinical studies or who are otherwise deemed unsuitable by the researchers. Withdrawal criteria include protocol violations such as detection of eligibility violations, use of any forbidden medication during the trial that could influence the study results, or occurrence of other significant protocol violations. In addition, subjects with serious adverse events, an allergic reaction to the investigational product, withdrawal of consent, and decision to terminate for reasons of the subject’s health will be withdrawn from the study. Symptomatic patients will be allowed to use antacids on demand in the posttreatment period. Antibiotics or other medications affecting the treatment results will be prohibited during the study period.

### Randomization and masking

Randomization will be conducted using a centralized, web-based randomization system managed by the Medical Research Collaborating Center (https://mrcc.snuh.org) of Seoul National University Hospital, which uses permuted block randomization with a concealed and varying block size. Only the researcher at the Medical Research Collaborating Center is able to know which number indicates which treatment arm. To ensure concealed allocation, an independent staff member will dispense consecutively numbered, identically designed treatment packs that contain sealed bottles of study drugs. Physicians who are unaware of treatment assignment will manage all study participants. Participants will not be blinded to group allocation.

### Procedures

The standard protocol for this study is shown in Fig. 3. Before enrollment, *H. pylori* infection status will be determined by a rapid urease test, urea breath test, histology, and/or bacterial culture. The patients will complete a standard questionnaire to collect complete demographic data, including age, sex, medical history, family history, history of smoking and alcohol consumption, and gastrointestinal symptoms. The patients will receive a printed handout that provides directions for taking the medications correctly and how best to adhere to treatment. The follow-up period of this study after randomization will be 8 weeks and will include two visits with each subject (first visit at 3 or 4 weeks after allocation, second visit 5–8 weeks after allocation). Adverse events and compliance will be evaluated at the first visit after allocation. At the second visit, the efficacy of *H. pylori* eradication therapy will be determined. In all subjects, a urea breath test will be conducted to assess *H. pylori* status at the fourth to sixth week after the end of *H. pylori* eradication therapy. A staff member blind to the eradication arm of each patient will perform the urea breath tests. The cutoff values will be set at 2% for the capsule urea breath test and 4.8% for the conventional urea breath test. Eradication will be defined as a negative result for the urea breath test. A Standard Protocol Items: Recommendations for Interventional Trials (SPIRIT) checklist is provided as an additional file (Additional file 1).

**Fig. 3 Fig3:**
[figure not shown]
Standard Protocol Items: Recommendations for Interventional Trials (SPIRIT) figure

### Tolerability and adherence

Drug tolerance and patient compliance will be evaluated at the end of treatment. Drug tolerance will be investigated by questioning patients about possible side effects, such as nausea, vomiting, dry mouth, diarrhea, constipation, rash, dizziness, disorientation, and candidiasis. Before treatment, the patients will be informed of the common adverse events associated with the study drugs and will be asked to record these symptoms during treatment in provided diaries. The adverse events will be assessed according to a 4-point scale: none, mild (discomfort annoying but not interfering with daily life), moderate (discomfort sufficient to interfere with daily life), and severe (discomfort resulting in discontinuation of eradication therapy) [24]. Incapacitating or life-threatening complications will be classified as serious and will be reported to a clinical research associate. Adherence to treatment will be assessed by providing all patients with a prestructured printed table with all dosages illustrated and then asking them to tick each time a pill was consumed and bring back the table along with any tablet not consumed, which will be counted. In cases of discrepancies between the structured printed table and residual medication, the latter will be taken into account to evaluate the patient’s adherence. Good compliance will be defined as the use of at least 80% of the total medication prescribed.

### Data management

The electronic case report form development and data management for this study will be performed using the Internet-based Clinical Research and Trial (iCReaT) management system (http://icreat.nih.go.kr), which is a data management system established by the Centers for Disease Control and Prevention, Ministry of Health and Welfare, Republic of Korea (iCReaT study number C160025).

### Monitoring

Because the known risks are minimal in this trial, no official data monitoring committee will be established in each study institution. Instead, to maintain the quality of this clinical trial, the clinical research associate will conduct regular monitoring by reviewing the informed consent form, case report form, investigator study file, compliance, serious adverse event, and data records. Monitoring will begin after the first participant completes the whole process of this study. Every institution where the trial is being conducted will be monitored using standard operating procedures while the trial is in process.

### Sample size

Several studies have demonstrated that the eradication rate of standard triple therapy is approximately 75% in Korea [25]. The eradication rate of sequential or concomitant therapy has been reported to be more than 80% [23, 26]. To obtain the optimal eradiation rate, an efficacy greater than 85% is needed for each treatment [27]. Therefore, we hypothesized that the eradication rate would be superior in the sequential or concomitant therapy groups, with a 10% difference compared with the rate for standard triple therapy (85% vs. 75%). To demonstrate this 10% difference in the eradication rate using a statistical power of 80% and with the assumption of a one-sided error rate of 0.025, the protocol requires at least 909 randomly assigned participants. The sample size in this trial was estimated according to the following formula:$$ n=\frac{{\left\{{\mathrm{z}}_{\alpha}\surd 2P\left(1-P\right)+{\mathrm{z}}_{\beta}\surd {P}_1\left(1-{P}_1\right)+{P}_2\left(1-{P}_2\right)\right\}}^2}{{\left({P}_1-{P}_2\right)}^2} $$

To allow for possible dropouts, defined as patients who fail to present or to follow the medication instructions, 1137 subjects will be required.

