### Statistical analysis

All efficacy analyses will be calculated for the intention-to-treat (ITT) and per-protocol (PP) populations. The ITT analysis will include all randomized patients who take at least one dose of the study medication. The patients whose infection status is unknown following treatment will be considered as treatment failures for the purposes of ITT analysis. The PP analysis will exclude patients with unknown *H. pylori* status following therapy and those with major protocol violations. The chi-square test, analysis of variance (ANOVA), or Fisher’s exact test, as appropriate, will be performed to compare demographic and baseline characteristics between treatment groups. The number and percentage of compliant patients will be tabulated according to the treatment regimen. Differences in compliance rates among treatment regimens will be assessed with 95% CIs. The chi-square test, ANOVA, or Fisher’s exact test, as appropriate, will be performed to compare adverse events and laboratory parameters between groups. The primary endpoint of the study is the *H. pylori* eradication rate after first-line treatment. The secondary endpoints are the frequency of adverse events, treatment compliance, and gastrointestinal symptomatic response after eradication.

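### The printed one-sided error rate of 0.025 does not give the printed 909 patients; 909 is the size for one-sided 0.0125 in each of two comparisons with control, so the significance threshold is ambiguous

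*Protocol article*

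**What the plan says.** The Trial design and study setting section describes a "multicenter, randomized, three-arm, superiority, parallel-group trial" with equal allocation: "Participants will be randomly allocated to the following three arms in a 1:1:1 ratio". One arm is the control (7-day standard triple therapy) and two are experimental (sequential and concomitant therapy).

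The objective joins the two experimental arms by an 'or'. The Abstract's Methods/design paragraph gives the aim as "to determine whether sequential or concomitant treatment is superior to standard triple therapy". The Sample size section repeats it as the hypothesis: "we hypothesized that the eradication rate would be superior in the sequential or concomitant therapy groups".

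The same section gives the design assumptions: eradication of 85% against 75%, power of 80%, and the error rate, "with the assumption of a one-sided error rate of 0.025". It prints a two-group formula with a single z-value for alpha. It then requires at least 909 randomised participants, raised to 1137 for dropout. It does not say whether 0.025 belongs to each comparison or to the two together.

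The Statistical analysis section opens with "All efficacy analyses will be calculated for the intention-to-treat (ITT) and per-protocol (PP) populations" and gives no threshold for the primary eradication comparisons. The only significance level in the article is therefore the one under Sample size.

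**The concern.** A claim that either of two regimens beats a common control gives two chances of a false positive. The level that matters is then the one for the pair of tests, and a reader must know whether a quoted 0.025 is per comparison or overall. The printed level and the printed sample size give different answers. An analyst who follows the text would declare superiority at z > 1.96; one who follows the sample size would require z > 2.24.

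A regimen with a one-sided p-value between 0.0125 and 0.025 would succeed under one threshold and fail under the other, unless a step-down rule applied and the other regimen had already passed. Both the Abstract and the main Discussion say that the trial will lead to revised first-line guidelines. The choice between the thresholds should not be open once the data are known. The Trial status section reports that recruitment is ongoing at 75% of target, so the article describes a trial in which this can still be settled.

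**Working it through.** **Inputs, all from the Sample size section unless noted.** P1 = 0.85 and P2 = 0.75, so P = 0.80 and the difference is 0.10. Power is 80%, so z_beta = 0.8416. Alpha is 0.025 one-sided. There are three equal arms (Trial design and study setting).

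**Formula.** The printed formula, with each square root read as covering its whole variance term:

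n = {z_alpha √[2P(1−P)] + z_beta √[P1(1−P1) + P2(1−P2)]}² / (P1−P2)²

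The variance terms are √(2 × 0.80 × 0.20) = √0.32 = 0.5657 and √(0.1275 + 0.1875) = √0.315 = 0.5612.

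**Step 1: which level reproduces 909?**

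- One-sided 0.0125 (z = 2.2414): (2.2414 × 0.5657 + 0.8416 × 0.5612)² / 0.01 = (1.2679 + 0.4724)² / 0.01 = 302.86, so 303 per arm and 3 × 303 = **909**. This matches exactly.
- One-sided 0.025 as printed (z = 1.9600): (1.1087 + 0.4724)² / 0.01 = 249.98, so 250 per arm and **750** in total. This does not match.

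Other variants at 80% power:

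| Variant | Per arm | Total |
|---|---|---|
| One-sided 0.025, continuity correction | 270 | 810 |
| One-sided 0.0125, continuity correction | 323 | 969 |
| One-sided 0.0125, unpooled variance | 300 | 900 |
| One-sided 0.025/3, pooled | 334 | 1002 |
| One-sided 0.05, pooled | 197 | 591 |

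None gives 909. One-sided 0.0125 is the same critical value as two-sided 0.025.

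**Step 2: dropout.** The article states no rate. If 20% is assumed, 909 / 0.80 = 1136.25, so **1137**, or 379 per arm. This matches the printed total, so the 909 is what was carried forward.

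**Step 3: error over the two comparisons.** With equal arms and a shared control, the two test statistics have correlation 0.5 when all three rates are equal. The chance of at least one false claim is 2 × alpha − P(both exceed the critical value).

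- At one-sided 0.025 each: 0.0500 − 0.0046 = **0.0454**, about 1.8 times 0.025. Simulation with one million replicates and 75% in every arm gave 0.0453 at 303 per arm and 0.0455 at 379.
- At one-sided 0.0125 each: 0.0250 − 0.0018 = **0.0232**. Simulation gave 0.0232 and 0.0235.

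**Step 4: power per comparison at 75% against 85%.** Power = Φ{[0.10√n − z_alpha × 0.5657] / 0.5612}.

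| n per arm | One-sided 0.025 | One-sided 0.0125 |
|---|---|---|
| 303 | 87.0% | 80.0% |
| 379 | 93.2% | 88.7% |

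The stated 80% power is met at 303 per arm with 0.0125. With 0.025 the same size would have 87.0%, which is not the figure in the text.

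**The case against.** The strongest objection is that the plan never says each arm will be tested at one-sided 0.025. That figure appears once, as a design assumption. The sample size suggests that the planners did split the level: 0.025 may be the overall one-sided rate divided between two comparisons, or a two-sided 0.05/2 labelled one-sided by mistake. Under either reading each comparison is tested at one-sided 0.0125 and the one-sided family-wise error is about 2.3%.

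This stands. A reader might infer that the trial will run two unadjusted tests and nearly double its false-claim rate. The article does not support that; the 4.5% follows only if the printed level is used for each comparison.

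It is also fair that a journal article need not carry the multiplicity procedure, the confidence level of the intervals, or the status of the sequential-versus-concomitant comparison. These may sit in a full protocol or analysis plan that is not shown, and their absence here is no fault.

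The objection does not remove the contradiction within the Sample size section. The article states a level, and that level does not produce its sample size. Both benign readings have to be worked back from 909, and a reader who takes the text at its word arrives at a different threshold.

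**Conclusion.** The point holds as an internal contradiction with a conditional consequence. For an 'either regimen' claim, the printed one-sided 0.025 gives 750 patients, and the printed 909 corresponds to one-sided 0.0125 per comparison. The two imply critical values of 1.96 and 2.24. The one-sided family-wise error would be about 4.5% under the first and about 2.3% under the second.

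It would go too far to conclude that the plan inflates its type I error, or that it lacks a multiplicity rule. The 909 points to an intended split, and the rule may be written elsewhere.

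The result rests on the stated rates and 80% power, the pooled formula without continuity correction, equal arms, and normal approximations. The power of 88.7% at 379 per arm also assumes that 75% and 85% hold in all randomised patients. The ITT rule counts patients of unknown status as failures, which could lower both rates.

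**What to change.** In the Sample size section, state that 0.025 is the overall one-sided error rate for the two comparisons with standard triple therapy. State also that each comparison is tested at one-sided 0.0125 (equivalently two-sided 0.025), and that this is the level used to obtain 303 per arm and 909 in total. Bonferroni at 0.0125 each is enough. Holm is an acceptable alternative: the smaller p-value at 0.0125 and, if that passes, the other at 0.025. Any full protocol or analysis plan should carry the same rule, fixed before the outcome data are examined.

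The cost is one sentence of text and a stricter threshold per comparison than a literal reading of 0.025. The sample size already covers it, with 80.0% power at 303 per arm and 88.7% at 379 under the stated rates. Matching the confidence level of the intervals to the test, and labelling the sequential-versus-concomitant comparison as secondary, would be helpful but are optional and not part of the error.

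### The stated sample-size inputs give 750 participants, not 909; the printed formula returns 909 at a one-sided error rate of 0.0125, not the stated 0.025

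*Protocol article*

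**What the plan says.** The Sample size section of the protocol article sets eradication rates of 75% for standard triple therapy and 85% for sequential or concomitant therapy. It states that, "using a statistical power of 80% and with the assumption of a one-sided error rate of 0.025, the protocol requires at least 909" randomized participants. It then says "The sample size in this trial was estimated according to the following formula" and prints the usual two-proportion expression, with pooled variance under the null hypothesis and separate variances under the alternative. After an allowance for dropouts, "1137 subjects will be required".

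Under Trial design and study setting, "Participants will be randomly allocated to the following three arms in a 1:1:1 ratio", so 909 means 303 per arm. The Abstract gives the aim as finding out whether either experimental regimen is superior to standard triple therapy, which makes two comparisons with one control. Neither the Sample size section nor the Statistical analysis section mentions dividing the error rate between them, and the Statistical analysis section gives no significance level for the primary comparison.

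**The concern.** Inputs, formula and result are all printed, so the result should follow from the inputs. It does not, and rounding cannot explain a gap of 159 participants (909 − 750).

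The practical issue is the significance level. The one error rate in the article is attached to a sample size that it does not produce. If the analysis takes 0.025 from this section and applies it to each comparison, each test is run at twice the level that reproduces 909. If 0.025 per comparison was meant, the power is misreported. A trial with two experimental arms against a shared control needs the per-comparison level to be unambiguous before the data are seen, and the Trial status section reports enrolment at 75% of target.

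**Working it through.** **Inputs, all from the protocol article**
- P1 = 0.85, P2 = 0.75, difference 0.10; mean P = 0.80 (Sample size)
- Power 80%, so z_β = 0.8416 (Sample size)
- One-sided error rate 0.025, so z_α = 1.9600 (Sample size)
- Three arms of equal size (Trial design and study setting)

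**Formula** (the printed one, each square root covering its whole variance term)

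n per arm = {z_α·√[2P(1−P)] + z_β·√[P1(1−P1) + P2(1−P2)]}² / (P1−P2)²

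- √(2 × 0.80 × 0.20) = √0.32 = 0.5657
- √(0.85 × 0.15 + 0.75 × 0.25) = √0.315 = 0.5612

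**Attempt to reproduce 909 with the stated inputs**
- 1.9600 × 0.5657 = 1.1087
- 0.8416 × 0.5612 = 0.4724
- (1.1087 + 0.4724)² / 0.01 = 1.5811² / 0.01 = 249.98, so 250 per arm
- 250 × 3 = **750**, against 909 stated; 909/750 = 1.21

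**The same formula at one-sided 0.0125** (z_α = 2.2414; two-sided 0.025 has the same critical value)
- 2.2414 × 0.5657 = 1.2679
- (1.2679 + 0.4724)² / 0.01 = 1.7403² / 0.01 = 302.86, so 303 per arm
- 303 × 3 = **909**, an exact match

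**Other routes to 909**

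| Calculation | Total |
|---|---|
| One-sided 0.025, 80% power, unpooled variance | 744 |
| One-sided 0.025, 80% power, arcsine | 744 |
| One-sided 0.025, 80% power, pooled variance | 756 |
| One-sided 0.025, 80% power, continuity correction | 810 |
| Printed formula, one-sided 0.025, 85% power | 858 |
| Continuity correction, one-sided 0.025, 85% power | 918 |
| Printed formula, one-sided 0.025, 90% power | 1005 |
| Printed formula, 0.025 split over three comparisons, 80% power | 1002 |
| Printed formula, one-sided 0.0125, 80% power | **909** |

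Dropout is not the explanation, since 909 is the figure before that allowance: 909/0.80 = 1136.25, which rounds up to 1137. The 1137 follows from 909 with an implied 20% loss and is not a separate error.

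**Power at 303 per arm**, with √303 = 17.407
- At 0.025: (0.10 × 17.407 − 1.1087)/0.5612 = 1.126, power 87.0%
- At 0.0125: (0.10 × 17.407 − 1.2679)/0.5612 = 0.842, power 80.0%

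**What the level changes in the analysis**
- Smallest significant difference at 303 per arm and a pooled rate of 80%, z_α × √(0.32/303) = z_α × 0.0325: 6.4 percentage points at 0.025 and 7.3 points at 0.0125.
- Chance of at least one false positive over the two comparisons, taking the test statistics as bivariate normal with correlation 0.5 (equal arms, shared control): 4.5% with each test at 0.025 and 2.3% with each at 0.0125.

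**The case against.** The strongest reply is that 0.025 may be the intended one-sided rate for the two comparisons together, with the halving carried out but not reported. Then 0.025 and 80% are both right and the sentence is incomplete rather than false; a journal article that condenses a longer protocol could easily lose that clause. This reading is plausible and fits the exact match at 0.0125. It does not remove the discrepancy: the formula takes one z_α, the text supplies one level for it, and that level does not yield 909.

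Four further points limit the claim:

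- The halving is inferred from a numerical match; the document does not state it.
- The uniqueness of 0.0125 holds for the printed formula at 80% power. Power to win both comparisons at one-sided 0.025 is about 79% by simulation at 303 per arm, which is near 80% but not a match, and the article describes no such criterion.
- The statistical analysis plan is not at hand and may fix the testing level, so an analysis at 0.025 per comparison is a risk and not a certainty.
- No reading leaves the trial short of patients.

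All four stand. They bear on the cause and the consequence, not on 750 against 909.

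**Conclusion.** The concern holds. The stated inputs give 250 per arm and 750 in total; the stated 909 is 21% higher. In the printed formula at 80% power, 909 corresponds to a one-sided error rate of 0.0125 per comparison. As written, therefore, either 0.025 is not the per-comparison level that was used, or 80% is not the power of 909, which would be 87.0%. An unreported split over two comparisons is the likely source, but that is an inference.

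The conclusion rests on the printed formula with its square roots read in the standard way, three equal arms, and 909 as the figure before dropout. Patient numbers are adequate on either reading. What needs correcting is the reported level or power: at 303 per arm, an observed difference between about 6.4 and 7.3 points would be significant under one reading and not under the other.

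**What to change.** The sponsor should confirm which error rate entered the calculation, whether it was one- or two-sided, and whether it applies to each comparison or to both together. Then amend the Sample size section.

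- **If the rate was split, as the match suggests:** state a one-sided error rate of 0.0125 per comparison (two-sided 0.025), obtained by Bonferroni from a family-wise one-sided 0.025 over the two comparisons with standard triple therapy, giving 303 per arm and 909 in total. Use the same per-comparison level in the Statistical analysis section and the statistical analysis plan.
- **If 0.025 per comparison was meant:** restate the requirement as 250 per arm (750 in total), or keep 909 and give its power as 87%.

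The 1137 can stay as long as 909 stays. The cost is one sentence in the protocol and a matching one in the analysis plan, with no extra patients. It should be settled before the outcome data are examined.
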